# A randomized controlled trial of WeChat-based cognitive behavioral therapy intervention to improve cancer-related symptoms in gynecological cancer survivors: study protocol

**DOI:** 10.1186/s12913-022-08443-y

**Published:** 2022-08-17

**Keywords:** Oncology, Quality of life, Cognitive behavioral therapy, Randomized controlled trial

## Abstract

**Background:**

Gynecological malignant patients often have significant psychological and physical problems. The feasibility and generalizability of traditional intervention method is low due to the high time and labor cost, large number of gynecological malignant tumor patients in China, as well as shortage of health professionals. Therefore, it is necessary to design an alternative, innovative, and easily accessible intervention method. This study aims to evaluate the effect of WeChat-based intervention on anxiety, depression and disease-related symptoms of patients with gynecological malignant tumors during rehabilitation.

**Methods:**

A single-blinded, randomized, controlled, parallel-group pre-test and repeated post-test design will be conducted. A total of 76 participants will be randomly divided into the intervention group and control group. Anxiety and depression, disease-related symptoms, coping ability, benefit finding and quality of life will be measured at baseline and repeated immediately after the intervention (test 1), 3 months (test 2) and 6 months (test 3) after the intervention.

**Discussion:**

As the first randomized controlled trial with rigorous research design for patients with gynecological malignant tumors in the rehabilitation stage in China, this study will provide evidences for the effectiveness of the WeChat platform during intervention of patients with gynecological malignant tumors in the rehabilitation stage. The results are helpful to further explore the effect of WeChat-based intervention on improving patients' anxiety and depression, disease-related symptoms, and quality of life.

**Trial registration:**

Chinese Clinical Trial Registry: ChiCTR2100053450, Registered 21 November 2021,http://www.chictr.org.cn/searchproj.aspx

## Background

Gynecological malignant tumor is a major disease threatening women's health, and has high incidence and high mortality [1]. There are many types of gynecological malignant tumors, among which ovarian cancer, cervical cancer, and endometrial cancer are the most common [2]. In recent years, the incidence rate has been increasing steadily, and the age of onset has gradually become younger. According to the report released by the International Agency for Research on Cancer (IARC), there were about 1,246,000 new cases of ovarian cancer, cervical cancer, and endometrial cancer and about 584,000 deaths in 2018 alone [1, 2]. The new cases of these three tumors in Chinese women is about 233,000, accounting for one fifth of the global cases, which greatly threatens the health and life of these patients [2, 3].

To treat gynecological malignant tumors, comprehensive treatment is generally needed, such as surgery, chemotherapy, or radiotherapy, which often leads to anatomical changes of the patient's reproductive system, menopause, vaginal dryness, hot flashes, and sexual intercourse pain [3]. The adverse effects result in damage to the reproductive, sexual, and urinary functions. Patients often have significant sexual psychological problems and body image disorders [4]. Moreover, the incidence of anxiety and depression was found to be high among these patients [5, 6]. Currently, the outcome for the treatment of malignant tumors is evaluated by not only the remission of clinical symptoms and the prolongation of survival time, but also the quality of life. Therefore, more attention should be paid to the psychological problems of patients with gynecological malignant tumors in the rehabilitation stage, in the purpose of alleviating symptoms and improving the patients’ quality of life.

A number of existing studies have shown that psychological intervention played a positive role in improving the sexual psychological problems and emotional disorders in patients with gynecological malignant tumors. Proper intervention satisfied the emotional and psychological needs of patients and improved the physical function by alleviating such symptoms as anxiety, depression, fatigue, pain, and insomnia [7–9]. Studies based in China have also confirmed the positive effect of psychological intervention for patients with gynecological malignant tumors [10, 11]. Recently, the cognitive behavior therapy (CBT), as a psychotherapy method in survival nursing, has attracted more and more attention. CBT plays an important role in group psychotherapy. By changing patients' incorrect cognition of the disease and conducting behavioral training, CBT helps the patients to establish reasonable cognition, change poor psychological state and negative coping style, thereby improving disease-related symptoms and the quality of life [12–15]. Many studies have shown that CBT is a beneficial treatment option for a variety of cancer patients [16–18]. Hersch et al. showed that CBT reduced psychological pain, anxiety, and depression [19]. However, current studies on CBT intervention for cancer patients are mainly focused on breast cancer, followed by prostate cancer [20]. Few studies have been carried out on patients with gynecological malignant tumors.

Moreover, traditional CBT interventions are carried out in a face-to-face setting. Studies have pointed out that due to cultural factors, most patients in China were unwilling to discuss sex psychology problems publicly [21, 22]. Stead et al. showed that only about a quarter of medical staff have been talked to about this problem. Thus, in many cases, the special psychological problems of patients with gynecological malignant tumors were not addressed [23]. Instead of face-to-face intervention, gynecological malignant tumor patients are more willing to participate in online support groups, due to the anonymity of discussion, which helped the patients feel comfortable talking about and solve these problems [24]. Further, the feasibility and generalizability of traditional intervention method is low due to the high time and labor cost, large number of gynecological malignant tumor patients in China, as well as shortage of health professionals. Therefore, it is necessary to design an alternative, innovative, and easily accessible intervention method. The development of internet has enable the possibility of convenient and accessible of online, virtual intervention, the Internet-based intervention can be conducted through multiple media formats to customize information, which saves participants' time and cost, and makes it easier to participate. Thus, internet-based intervention is an innovative and convenient intervention method, and has the ability to reach more target patients [25, 26]. Internet cognitive behavioral therapy (ICBT) produced the same results as face-to-face therapy in terms of mental health improvement. ICBT is being increasingly adopted in the study of physical health of patients with chronic diseases [27, 28]. A review by Andersson et al. showed that the effects of ICBT and face-to-face CBT on a series of mental and physical diseases were the same, which provided evidences for the adoption of ICBT [29].

In China, WeChat is the most widely used social network platform. At present, there are 902 million active users every day, and each user spend an average of 66 min on the platform every day [30]. WeChat has many different functions, such as private or group texts or voice messages, video calls or meetings, electronic document transmission, subscription and browsing of public accounts and information publishing [31, 32]. Because WeChat has a variety of interactive functions and a large amount of users, and is convenient, timely, and affordable [32], it has been slowly changing the way people receive information. It breaks the time and space limitations of traditional classrooms, improves autonomous learning, and strengthens cooperation with peers [33]. WeChat has been used for behavioral intervention and disease prevention and control, such as cancer, malaria, asthma, chronic sinusitis, diabetes and weight loss [34–39]. Some studies have used WeChat-based group intervention for malignant tumor patients. The attrition rate of participants was relatively low and the acceptability among users was good. Some patients said that they have found a sense of belonging in the patient group, and have "people and places that can speak their hearts". As a result, both online and offline communication was very active [40]. WeChat can optimize the communication between patients and medical staff [32],and when doctors withdrew from the WeChat group after the group intervention, group members can still maintain interactive communication in the WeChat group. Through the platform, the members spontaneously organized offline collective outings and other activities to provide continuous psychological support between group members [40]. However, there is still no study on the effect of WeChat on patients with gynecological malignant tumors in the rehabilitation stage. Therefore, the objective of the present study is to explore the WeChat-based CBT(WCBT) intervention model. By carrying out psychological intervention and follow-up management of patients with gynecological malignant tumors through WeChat, its impact on the patients’ physical and psychological symptoms will be explored.

## Methods/design

### Aims

The objective of this study was to evaluate the effect of CBT based on the WeChat platform on anxiety, depression, and disease-related symptoms of patients with gynecological malignant tumors in the rehabilitation stage, thereby establishing an intervention model to improve the patient’s coping ability, benefit finding and quality of life. The study hypothesizes that compared with the control group at baseline, test 1, test 2 and test 3, patients in the intervention group will report statistically significant:The degree of anxiety and depression is decreased;Disease-related symptoms are reduced;Coping ability, benefit finding and quality of life are improved.

### Study design

#### Trial design

A single-blinded, randomized, controlled, parallel group pre-test, and repeated post-test design will be conducted to investigate the effect of WeChat-based Cognitive behavioral therapy for Chinese gynecological cancer survivors.

#### SPIRIT statement

The study follows the SPIRIT 2013 Statement and the guidelines for the Standard Protocol of Clinical Trials [41]. Figure 1 is available for this protocol. The Consolidated Standards of Reporting Trials (CONSORT) [42] flowchart is presented in Fig. 2.

**Fig. 1 Fig1:**
[figure not shown]
SPIRIT schedule of enrolment, interventions, and assessments

**Fig. 2 Fig2:**
[figure not shown]
CONSORT flowchart of the study. Note: HADS: Hospital Anxiety and Depression Scale; FACT-G: Functional Assessment of Cancer Therapy—General; MSAS-SF: The Chinese version of the Memorial Symptom Assessment Scale- Short Form; Mini-MAC: Mini-Mental Adjustment to Cancer Scale; BFS: Benefit-Finding of Cancer Patients Scale

#### Study setting and participants

The study will be conducted in a tertiary public hospital affiliated to a university in China. Patients with gynecological malignant tumors (i.e., cervical cancer, endometrial cancer, and ovarian cancer) will be recruited in the outpatient department of the hospital.

##### Inclusion criteria

(1) patients with pathologically confirmed cervical cancer, endometrial cancer, and ovarian cancer; (2) patients who have completed surgery and / or radiotherapy and chemotherapy and have entered the rehabilitation stage; (3) Age 18–65 years; and (4) Kamofsky performance status (KPS) score > 60 points [43].

##### Exclusion criteria

(1) patients with history of mental illness, material dependence or consciousness disorder; (2) patients with hearing and visual impairment; and (3) patients undergoing any form of psychotherapy.

##### Drop-out criteria

(1) the disease progressed to a great extent during the intervention (tumor recurrence or metastasis); and (2) Other forms of psychotherapy are received during the study.

Sample size will be estimated based on previous research with a medium to small effect size [44]. With a power of 0.90, an alpha set at 0.05, and an effect size of 0.47 for the primary outcome of FACT-G scores, each group will be 29 women [21]. We estimate a 30% attrition rate based on an attrition rate of 28.8% in previous research [45]. A minimum of 76 women (38 in each group) are required.

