#### Recruitment

The participants will be recruited from the gynecology outpatient department. Posters and flyers about this study will be posted and distributed in the outpatient center. An information sheet about the study will be given to the patients who verbally expressed their intention of participation. In order to make sure that they have enough time to read the information sheet, discuss with family members, and make the final decision, one week will be given to the patients. If a patient agrees, the contents, procedures, and rules of the study will be explained to her, and she will be asked to sign an informed consent. At the same time, oncology experts of this study will review the participants' medical records to obtain information about disease diagnosis, pathology, past and current cancer treatment, and patients' treatment compliance. Subjects will be screened according to the inclusion criteria. The recruitment period is expected to last for 3 months. Data will be collected before randomization (baseline), immediately after intervention (test 1), 3 months after intervention (test 2) and 6 months after intervention (test 3). The trial will be conducted in accordance with the Declaration of Helsinki and will take place from Jun 1, 2022 to Dec 31, 2023.

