### Intervention

Patients in the control group will receive routine outpatient follow-up, during the visits, they will be provided general health recommendation, brief medication and exercise guidance, and information related to mental health. In addition, telephone follow-up will be carried out once a month. The patients are allowed to ask questions related to the disease through WeChat or mobile phone, yet they cannot participate in the online educational intervention.

For the intervention group, patients will receive group CBT for 10 weeks, carried out by psychiatrists, psychological counselors, and oncology nurses who had received CBT training. The details of intervention are described in Table 1. For the purpose of better communication, 38 patients in the intervention group were divided into three WeChat groups (12–13 patients in each group). The same intervention scheme was used in the three groups. Group CBT professionals will be invited to evaluate and supervise the intervention process.

**Table 1 Tab1:** The details of intervention

	Intervention Group	Control Group
Service	WCBT + routine care	Routine care
Provider	Researchers	Doctors and nurses
Place	Web environment	Hospital outpatient
Form	WeChat platform	Face-to-face
Contents	Cognitive reconstruction; Cognitive behavioral therapy; Support expression	Regular follow-up
Duration and frequency	The total intervention time not less than 10 weeks	Follow up at least twice
Assessment	Baseline (pre-intervention) Test 1 (immediately after intervention) Test 2 (3 months after intervention) Test 3 (6 months after intervention)	Baseline (pre-intervention) Test 1 (immediately after intervention) Test 2 (3 months after intervention) Test 3 (6 months after intervention)

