### Outcome measurements

#### Primary outcomes

Hospital Anxiety and Depression Scale (HADS) [46]. There are 14 items, including 7 items on anxiety and 7 items on depression. A score of 0–7 means the participant is asymptomatic, 8–10 is suspicious, and 11–21 means symptomatic. Cronbach α coefficients of the total scale, as well as the anxiety and depression subscales are 0.88, 0.81 and 0.81, respectively [49].

Memorial Symptom Assessment Scale–Short Form (MSAS-SF), which is used to evaluate the characteristics of physical and psychological symptoms of cancer patients [50]. There are 32 items consisting of 2 subscales: physical symptoms and psychological symptoms. The incidence and frequency of each symptom will be evaluated. The Cronbach's alpha coefficient ranged from 0.84 to 0.91 [51].

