### Statistical analysis

All data were analyzed using the Statistical Package for Social Sciences 22.0(SPSS Inc., Chicago, IL, USA). Two researchers will carry out data analyses.Participants’ characteristics and outcome scores were summarized using means ± standard deviation (SD) or medians [interquartile ranges (IQR)] for continuous variables or frequencies (percentages) for categorical variables. Baseline characteristics and outcomes were compared using independent samples t-test or Mann–Whitney U test from continuous variables and chi-squared test for categorical variables between the intervention and control group. *p* values < 0.05 were considered statistically significant. All analyses will be conducted on an intention-to-treat basis.

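### The drop-out criteria act after randomisation on events related to the primary outcomes, and the protocol does not reconcile them with its intention-to-treat statement

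*Protocol article*

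**What the plan says.** The Drop-out criteria section of the protocol article lists two events. The first is that "the disease progressed to a great extent during the intervention (tumor recurrence or metastasis"). The second is "Other forms of psychotherapy are received during the study". They differ in reach: the first is limited to the intervention period, which lasts 10 weeks according to the Intervention section, and the second covers the whole study.

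Neither is an entry rule. Psychotherapy at entry is handled separately under Exclusion criteria ("patients undergoing any form of psychotherapy").

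The Statistical analysis section states: "All analyses will be conducted on an intention-to-treat basis". It makes no exception.

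The Primary outcomes section names HADS (anxiety and depression) and MSAS-SF, "which is used to evaluate the characteristics of physical and psychological symptoms of cancer patients". Assessments are planned before randomisation and then "immediately after intervention (test 1), 3 months after intervention (test 2) and 6 months after intervention (test 3"). Under Data collection, the three post-baseline assessments are electronic questionnaires sent through WeChat.

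**The concern.** Intention to treat means that every randomised woman is followed and analysed in her allocated arm, whatever happens to her afterwards. A rule that drops women because of something that happened after randomisation pulls the other way unless the protocol confines it to stopping the intervention. This one does not.

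The two events are not neutral. Recurrence bears directly on anxiety, depression and symptom burden, and women who seek psychotherapy are likely to be the more distressed. Losing them leaves a selected group whose scores look better than those of the group that was randomised.

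A later analysis plan can choose how to handle missing scores. It cannot restore questionnaires that were never sent because a woman had been classed as dropped out. The meaning of the criteria therefore has to be settled before follow-up.

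**Working it through.** **1. The text.** No arithmetic is needed for the conflict itself.

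- Drop-out criteria: two events that can only occur after entry, with no statement of what the woman drops out of (intervention, assessments or dataset).
- Statistical analysis: intention to treat, without exception.
- Elsewhere: no sentence keeps these women in follow-up or in the analysis, and none removes their data.
- Sample size paragraph: 29 per group is inflated for 30% attrition, 29 × 1.30 = 37.7, giving 38 per group and 76 in total. This fits counting drop-outs as lost but does not prove it. If 30% were lost, 76 × 0.70 = 53.2 women would remain. The inflation replaces numbers; it does not correct for who is lost.

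**2. Size of the possible bias.** The documents give no removal rates, so every rate below is an assumption. Scores are in SD units, higher is worse, and there is no true treatment effect. Outside psychotherapy is given no effect of its own.

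*Model A: removal in controls only.* A fraction p of controls is removed and no intervention women are.

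If the most distressed p leave, the retained control mean improves by φ(z)/(1 − p), where z is the (1 − p) normal quantile:

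- p = 5%: 0.1031/0.95 = 0.11 SD
- p = 10%: 0.1755/0.90 = 0.20 SD (0.195)
- p = 15%: 0.2332/0.85 = 0.27 SD

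If instead the log-odds of removal rise by 1 per SD of distress, numerical integration gives 0.05, 0.09 and 0.13 SD for the same three rates.

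*Model B: removal in both arms.* Proneness to removal correlates r with a worse score, and the most prone are removed. With g(p) = φ(z)/(1 − p), the bias is r × [g(p control) − g(p intervention)]. The values are g(5%) = 0.109, g(10%) = 0.195, g(20%) = 0.350 and g(30%) = 0.497.

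| Removed, control vs intervention | Difference in g | Bias for r = 0.3 to 0.7 |
|---|---|---|
| 10% vs 10% | 0 | 0 |
| 10% vs 5% | 0.086 | 0.03 to 0.06 SD |
| 20% vs 5% | 0.241 | 0.07 to 0.17 SD |
| 30% vs 10% | 0.302 | 0.09 to 0.21 SD |

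A simulation of model B agrees to within about 0.005 SD.

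**3. Reading.** Unequal removal gives roughly 0.03 to 0.27 SD over the two models. The top of that range needs one-sided removal of exactly the most distressed 15% of controls. Equal removal gives about zero. If more controls are removed, the bias runs against the intervention; if more intervention women are removed, it reverses.

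**The case against.** The strongest reply is that the protocol never says follow-up stops or data are deleted. Read literally, an intention-to-treat statement covering all analyses includes these women, and the criteria may mean no more than leaving the intervention. A condensed article may also leave the handling of such events to a fuller document. The first part stands: a reader might infer that these women's later questionnaires are certainly lost and that intention to treat cannot be carried out, and the text does not go that far. The second part does not dispose of the point. The article states a rule and a principle that pull apart, and nothing in it limits the rule to treatment.

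A reader might also infer that removal is tied to arm and hides a benefit. There is a reason to suspect it, since "Patients in the control group will receive routine outpatient follow-up" and cannot join the online educational intervention. But no rate by arm is given, and the Randomization and blinding section says participants are blinded. That is hard to credit for group CBT over WeChat, but it is the stated position. The Exclusion criteria also keep out women with a history of mental illness, which may lower the use of outside psychotherapy. For recurrence, the documents give no reason to expect a difference between arms, and the criterion is limited to the intervention period.

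It is tempting, too, to express the shift as a share of the planned effect of 0.47. That figure is an effect size for FACT-G, which the protocol lists under Secondary outcomes, whereas the calculation concerns distress. The ratio would mix outcomes and is not used here.

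Finally, deleting the criteria outright might also delete a rule for stopping the intervention. That objection stands, and the fix avoids it.

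**Conclusion.** The point holds as an unreconciled conflict between two stated parts of the protocol. Applied as written, the drop-out criteria would lose women for reasons related to HADS and MSAS-SF, and the analysis would no longer be a full intention-to-treat comparison.

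That the loss would be outcome-related follows from the nature of the events. That it would differ by arm is plausible for psychotherapy but undocumented. The 0.03 to 0.27 SD range shows what unequal removal could do under assumed rates; it is not an estimate for this trial, and near zero is equally consistent with the documents. Nor is it the gain to be expected from the fix, because the calculation gives outside psychotherapy no effect. The documents do not support a claim that the randomised comparison is already broken, or that the bias has a known direction.

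It still deserves correction before follow-up: with 38 women per arm, 10% is about four women (0.10 × 38 = 3.8), and assessments not collected cannot be recovered.

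**What to change.** Reconcile the Drop-out criteria and Statistical analysis sections with wording to this effect:

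- Meeting a drop-out criterion does not end assessment. The woman completes tests 1 to 3 unless she withdraws consent.
- She is analysed in the arm to which she was randomised.
- Recurrence or metastasis and outside psychotherapy are recorded, with dates, as intercurrent events.
- Any analysis that excludes these women is labelled a sensitivity analysis.

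Whether such a woman continues the intervention is a separate matter for the investigators; the wording should leave it to them and say so.

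The cost is a short amendment and slightly more follow-up effort, small because tests 1 to 3 are online questionnaires. The other consequence is interpretive: the effect estimate will include any effect of psychotherapy obtained outside the trial, which could narrow the contrast if more controls use it and it helps. The report should state this.

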#### Secondary outcomes

Functional Assessment of Cancer Therapy–General (FACT-G). It is a general scale used to evaluate the cancer patients' quality of life. There are 27-item consisting of 4 subscales: physical, social, emotional and functional wellbeing (total score of 0–108; higher scores = better QoL), Cronbach α is 0. 88, 0. 82, 0. 87, 0. 83,respectively [52].

Coping, which is measured with the mini-Mental Adjustment to Cancer Scale (mini-MAC) [53], a 29-item scale yielding 5 factors: Fighting Spirit, Helplessness/Hopelessness, Anxious Preoccupation, Fatalism, and Cognitive Avoidance. Items are responded to on a 4-point scale ranging from ‘definitely does not apply’ to ‘definitely does apply’.

Benefit Finding of Cancer Patients Scale(BFS). The scale was adapted by Weaver et al. [54], which was employed in prior studies of gynecological cancer patients [55]. Benefits included both interpersonal and intrapersonal changes from cancer. Higher scores indicated perceiving more benefits from cancer.

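### The sample size rests on FACT-G, called the primary outcome, while the outcomes section makes HADS and MSAS-SF primary; the stated 90% power does not apply to the declared primaries

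*Protocol article*

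**What the plan says.** The sample-size calculation stands in the Protocol article under Drop-out criteria. It sets "With a power of 0.90, an alpha set at 0.05" and uses "an effect size of 0.47 for the primary outcome of FACT-G scores". From these it reaches 29 women per group, then 38 per group (76 in total) after a 30% allowance for attrition.

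The section Primary outcomes names two scales. The first entry reads "Hospital Anxiety and Depression Scale (HADS) [46]. There are 14 items, including 7 items on anxiety and 7 items on depression"; the second is "Memorial Symptom Assessment Scale–Short Form (MSAS-SF), which is used to evaluate the characteristics of physical and psychological symptoms of cancer patients". FACT-G is not there. It is the first entry under Secondary outcomes: "Functional Assessment of Cancer Therapy–General (FACT-G). It is a general scale used to evaluate the cancer patients' quality of life".

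The Aims section states the objective as "to evaluate the effect of CBT based on the WeChat platform on anxiety, depression, and disease-related symptoms of patients with gynecological malignant tumors", and names quality of life afterwards, with coping and benefit finding, as something the resulting intervention model should improve. The abstract's statement of aim covers anxiety, depression and symptoms only.

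**The concern.** A power statement is useful only for the outcome on which the trial will be judged. Here the outcome that was sized and the outcomes declared primary are different scales, and the text gives FACT-G two incompatible ranks.

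Two things are at stake. First, a reader cannot tell what difference on HADS or MSAS-SF the trial was designed to find, so a null result on either would be hard to interpret. Second, while both labels stand, a later report could cite one section to lead with FACT-G or another to lead with HADS and MSAS-SF. The protocol should close that choice before anyone sees results by group.

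**Working it through.** **Step 1. Set the sections side by side.**

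| Place in the Protocol article | HADS | MSAS-SF | FACT-G |
|---|---|---|---|
| Sample-size paragraph (under Drop-out criteria) | not mentioned | not mentioned | called primary; effect size 0.47 |
| Primary outcomes | listed | listed | absent |
| Secondary outcomes | absent | absent | listed first |
| Aims and abstract | anxiety and depression are the stated target | symptoms are the stated target | quality of life is downstream in Aims, absent from the abstract's aim |

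The first row cannot be squared with the second and third. The headings carry the ranking, and they are intact in the text.

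**Step 2. Look for a power basis for the declared primaries.** The article gives no effect size, standard deviation, power or sample size for HADS or MSAS-SF. The sample-size paragraph also speaks of a medium to small effect, but ties it to no scale. The only outcome-specific figure is 0.47, for FACT-G.

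**Step 3. Try to reproduce the plan's own figure.** Inputs from the sample-size paragraph: power 0.90, alpha 0.05, effect size 0.47. The 1:1 ratio comes from Randomization and blinding. Assumptions: 0.47 is a standardised mean difference d and the test is two-sided; neither is stated.

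n per group = 2 × (1.960 + 1.282)² / d² = 2 × 10.51 / 0.2209 = 95.1, so 96 (97 with the t distribution).

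The plan states 29, so it is not reproduced. A one-sided test gives 78. Reading 0.47 as Cohen's f (d = 0.94) gives 24. A figure near 29 appears only with inputs that the document does not state, such as adjustment for a baseline value correlated at about 0.83 (30 per group). With 29 per group and d = 0.47, a two-sided t-test has 42% power.

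This is a separate defect from the mislabelled outcome. It matters here because it rules out relabelling as a sufficient repair.

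**Step 4. What 76 women can detect on any scale.**

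- The plan's inflation: 29 × 1.3 = 37.7, so 38 per group.
- Completers if 30% are lost: 38 × 0.7 = 26.6, about 27 per group.
- Detectable d, normal approximation: (1.960 + 1.282) × √(2/27) = 3.242 × 0.272 = 0.88. The t distribution gives 0.90 at 90% power and 0.78 at 80% power.
- If the two primaries split alpha equally, at 0.025 each: (2.241 + 1.282) × 0.272 = 0.96 at 90% power; the t distribution gives 0.98.

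These are statements about the sample size. They say nothing about how large the effect on HADS or MSAS-SF will be.

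**The case against.** The strongest defence is that the sentence ends with a citation and the paragraph says that sizing follows previous research. The words about FACT-G may describe the cited study's primary outcome, carried over without care. On that reading the protocol has one hierarchy, HADS and MSAS-SF, supported by the headings, the aims and the abstract, and the risk of choosing the primary outcome afterwards is smaller. The cited study is not at hand, so this cannot be settled. Even if it is right, the 90% power was calculated for a scale that this trial ranks as secondary, and nothing in the article justifies carrying 0.47 over to HADS or MSAS-SF.

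A second defence is that a baseline-adjusted or repeated-measures analysis could need fewer women than a t-test. That is true, and a fuller document may specify one. The article's Statistical analysis section names the independent-samples t-test or the Mann–Whitney test for comparing groups, and no such analysis would resolve which outcome is primary.

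A reader might go further and infer that the trial is underpowered for HADS and MSAS-SF. The documents do not support that. They give no expected difference or standard deviation for either scale, so any required sample size for them would rest on an effect chosen by the reader. An analysis plan or full protocol not shown here could supply those assumptions, but it would not remove a contradiction printed in this article.

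**Conclusion.** The contradiction is real and should be corrected. The sample-size paragraph treats FACT-G as primary; the outcomes section ranks it secondary and makes HADS and MSAS-SF primary, and the aims side with the outcomes section. The stated 90% power therefore does not apply to the declared primary outcomes, whose power is unstated rather than shown to be low.

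The size can be given only as a detectable difference: about 0.90 standard deviations at 90% power. This assumes 27 completers per group with outcome data, a two-sided t-test at 0.05 and no covariate adjustment. Dividing alpha between two primaries raises it; adjusting for a predictive baseline value lowers it.

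**What to change.** Before unblinding:

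1. State one outcome hierarchy in every section. The aims point to HADS and MSAS-SF as primary.
2. If FACT-G stays secondary, delete the phrase that calls it primary from the sample-size paragraph.
3. Replace the power statement with the power or detectable difference for HADS and for MSAS-SF at the planned 76 women. Give the assumed effect, standard deviation, test, sidedness and number of completers. State how the two primaries share alpha, or that success is required on both.
4. If FACT-G is made primary instead, bring the aims into line and still redo the calculation, because 0.47 read as d needs about 96 per group and the plan states 29.
5. Check that the registry entry agrees. It was not available for this review, so no discrepancy is alleged.

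The cost is a wording amendment, a redone calculation and probably a less favourable stated power. HADS, MSAS-SF and FACT-G are already collected at every assessment, so fieldwork does not change as long as the power is restated at 76. Enlarging the trial would be a different decision, with real consequences for a single hospital and a planned recruitment period of three months.
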